### Study procedures and visits

An overview of consecutive study procedures and visits for participants is listed in Fig. 2.

**Fig. 2 Fig2:**
[figure not shown]
Participant timeline. Black circles (●) indicate neonates with a prenatal CCHD diagnosis. White circles (○) indicate neonates with a postnatal CCHD diagnosis. *In included subjects from the Erasmus Medical Center Rotterdam and University Medical Center Utrecht. **In the first 24 subjects with a prenatal CCHD diagnosis in UMC Utrecht. aEEG, amplitude-integrated electroencephalography; Bayley-III-NL, Bayley Scales of Infant and Toddler Development - Third Edition - Dutch Norms; CCHD, critical congenital heart disease; h, hours; HTA, health technology assessment; MRI, magnetic resonance imaging; NIRS, near-infrared spectroscopy; TAPQoL, TNO-AZL preschool children’s health-related quality of life

#### Brain MRI

Brain MRI will be performed pre- and postoperatively on a 1.5- or 3.0-T MRI scanner to assess the presence, severity, and volume of ischemic and hemorrhagic parenchymal brain lesions. The MRI scanning protocol includes at least T1-, T2-, diffusion-, and susceptibility-weighted imaging and MR venography [8, 39, 41]. Preoperative MRI will take place within 4–7 days after birth or at least preoperatively. Postoperative MRI will take place preferably within 5–10 days after surgery or at least within 1 month following CPB.

#### Echocardiography

Echocardiography will also be executed pre- and postoperatively, preferably on the same day as the brain MRI, to evaluate potential cardioprotective effects of allopurinol [57]. The echocardiography protocol emphasizes on cardiac systolic and diastolic function, including global ventricular function, ejection (Simpson’s biplane method or four-dimensional) and shortening fraction, ventricular dimensions, velocity over the cardiac valves (pulsed/continuous wave Doppler), cardiac valve insufficiency, longitudinal strain and tissue Doppler imaging (myocardial deformation indices), and systolic and diastolic pulmonic vein flow [44].

#### Neuromonitoring

Brain function will be assessed by amplitude-integrated electroencephalography (aEEG) and oxygenation by near-infrared spectroscopy (NIRS) at defined time points after birth (0–3, 3–6, 6–12, 12–24, 24–36 h) and surgery (0–3, 3–6, 6–12, 12–24, 24–48, 48–72 h) [45, 47]. Dominant background pattern and changes in background pattern over time (continuous normal voltage, discontinuous normal voltage, burst suppression, continuous low voltage, flat trace) and presence of sleep-wake cycling and seizure activity (absent, single seizure, repetitive seizures, status epilepticus, including response to anti-epileptic drugs) will be identified with aEEG [45]. The mean regional cerebral oxygen saturation (rScO_2_), lowest rScO_2_ (%), and duration of rScO_2_ < 45% will be assessed by NIRS [47]. Neuromonitoring will be performed after birth with continuation for at least 24 h, and after surgery with continuation for at least 48 h.

#### Neurodevelopmental follow-up

At 3 months, general movements will be systematically recorded and assessed, including a detailed score of the entire motor repertoire, using the motor optimality score [49, 50]. At 24 months, motor, cognitive, and language development will be scored with the Bayley Scales of Infant and Toddler Development - Third Edition, Dutch Norms (Bayley-III-NL), and neurological examination to objectify possible cerebral palsy is performed. An average Bayley-III-NL score is 100, one standard deviation above or below the mean concerns 15 points [52]. Children with an underlying syndromic disorder will be analyzed separately, as this group is expected to score lower on neurodevelopmental outcomes [58].

#### Cost measurement

The use of healthcare resources, productivity losses of parents, and expenses borne by families will be collected with questionnaires among parents during follow-up visits at 3 and 24 months. In addition, we will monitor the length of intensive care stay and hospitalization during the trial and estimate the costs associated with hospitalization using standard unit prices from the Dutch guidelines for health economic evaluation.

#### Quality of life

The TNO-AZL Preschool Children’s Health-Related Quality of Life Questionnaire for parents is a systematic, valid, and reliable tool that will be used to score the quality of life of CCHD infants at the age of 24 months [53].

#### Pharmacokinetics of allopurinol

In the first 24 neonates with a prenatal CCHD diagnosis in the UMC Utrecht, blood samples will be collected postnatally and perioperatively for pharmacokinetic evaluation of allopurinol. It is expected—depending on the randomization—that approximately 12 of these neonates received allopurinol PFI and 12 mannitol-placebo PFI. This analysis will be performed to extend knowledge on the current pharmacokinetic data of allopurinol, oxypurinol, hypoxanthine, xanthine, and uric acid and to establish if expected target concentrations of allopurinol > 2 mg/L are reached in CCHD neonates [54]. Blood sampling will be combined with clinically indicated samples and will be taken from pre-existent arterial or venous access lines.

#### Redox state

In order to quantify and assess the antioxidant properties of allopurinol after ischemia-reperfusion events and correlate redox biology to ischemia-reperfusion status, additional blood and urine samples of included subjects from the Erasmus MC Rotterdam and UMC Utrecht will be collected at fixed intervals (umbilical cord, preoperatively, 6 h postoperatively, and on days 1, 2, and 4 postoperatively). Using enzyme-linked immunosorbent assay, ROS analyses will be performed, including hypoxic tissue injury, overall redox and antioxidant state, lipid peroxidation, protein oxidation, and nitrosative state. Mass spectrometry will be used to determine allopurinol, oxypurinol, non-protein bound iron, and XO levels. The resultant molecular framework will provide a redox biological basis for allopurinol suppletion and couple the restoration of the redox imbalance to cerebral hypoxia-ischemia.

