#### Prenatal group

In neonates that are diagnosed with CCHD before birth, allopurinol PFI or mannitol-placebo PFI 20 mg/kg body weight per administration will be administered early postnatally (within 45 (max. 60) min after birth and 12 h after the first dose), preoperatively (12 h prior to cardiac surgery), intraoperatively (at the start of CPB), and postoperatively (24 h after surgery) (Fig. 1).

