#### Postnatal group

Neonates in whom CCHD is diagnosed after birth will only receive the pre-, intra-, and postoperative doses of allopurinol PFI or mannitol-placebo PFI (Fig. 1).

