#### Secondary outcomes

The secondary outcomes that will be compared between the allopurinol and mannitol-placebo groups are presented in Table 1 and include the five elements (domain, specific measurement, specific metric, method of aggregation, and time point) as described by Zarin et al. and Saldanha et al. [55, 56].

**Table 1 Tab1:** Secondary outcomes

Domain	Specific measurement	Specific metric	Method of aggregation	Time point
Brain injury severity	Brain injury severity score, determined by the assessment of brain injury on MRI in the deep gray matter, white matter, cortex, and cerebellum [39, 40].	Preoperative brain injury severity score, postoperative brain injury severity score, and change between pre- and postoperative brain injury severity score	Mean (and SD) or median (and IQR) per group	Preoperative (4–7 days after birth) Postoperative (5–10 days after surgery or at least within 1 month after surgery)
White matter injury volume	White matter injury volume (mm^3^), determined by manual segmentation with 3D-Slicer or ITK-SNAP 2.0 [41–43].	Preoperative white matter injury volume, postoperative white matter injury volume, and change between pre- and postoperative white matter injury volume	Mean (and SD) or median (and IQR) per group	Preoperative (4–7 days after birth) Postoperative (5–10 days after surgery or at least within 1 month after surgery)
Echocardiographic systolic and diastolic function	Echocardiographic assessment of global ventricular function (normal, mildly reduced, moderately reduced, severely reduced); ejection fraction (%); shortening fraction (%); ventricular dimensions (mm, *Z*-score corrected for BMI); velocity over the cardiac valves, i.e., *V*peak (m/s) and *V*mean (m/s); cardiac valve insufficiency (no, mild, moderate, severe); longitudinal strain (%) and tissue Doppler imaging (myocardial deformation indices (m/s)); and systolic and diastolic pulmonic vein flow (m/s) [44].	Preoperative echocardiographic measurements, postoperative echocardiographic measurements, and change between pre- and postoperative echocardiographic measurements	Distribution per group for categorical variables and mean (and SD) or median (and IQR) per group for continuous variables	Preoperative (4–7 days after birth) Postoperative (5–10 days after surgery or at least within 1 month after surgery)

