Cost-effectiveness of allopurinol	Motor, cognitive, and language composite score of the Bayley-III-NL [52] and healthcare and societal costs. Healthcare and societal costs will be determined with the Dutch guidelines for health economic evaluation.	Bayley-III-NL score, healthcare, and societal costs	Cost per point improvement in neurodevelopmental outcome per group	24 months
Pharmacokinetic evaluation of allopurinol	Allopurinol, oxypurinol, hypoxanthine, xanthine, and uric acid levels (mg/L) will be measured in blood samples collected around birth and surgery in 24 patients with a prenatal diagnosis [20, 32, 33, 54].	Allopurinol, oxypurinol, hypoxanthine, xanthine, and uric acid levels (mg/L)	Mean (and SD) or median (and IQR)	Postnatal (umbilical cord and 15–60 min, 4 h, 12 h, 13–14 h, 24 h, 36–48 h, and 96–168 h after birth) Perioperative (0–3 h before dose 3, 1–3 h after dose 3, 0–1 h before dose 4, at the end of CPB, 4 h after surgery, 0–3 h before dose 5, 1–3 h after dose 5, and 48 h after surgery)
Redox and antioxidant state of allopurinol	Enzyme-linked immunosorbent assay will be used to measure hypoxic tissue injury, overall redox and antioxidant state, lipid peroxidation, protein oxidation, and nitrosative state. Mass spectrometry will be used to determine allopurinol, oxypurinol, non-protein bound iron, and xanthine oxidase levels (mg/L) [12].	Hypoxic tissue injury, overall redox and antioxidant state, lipid peroxidation, protein oxidation, and nitrosative state Allopurinol, oxypurinol, non-protein bound iron, and xanthine oxidase levels (mg/L)	Mean (and SD) or median (and IQR) per group	Postnatal (umbilical cord) Perioperative (directly before surgery and 6 h, 1 day, 2 days, and 4 days after surgery)

*Abbreviations*: *aEEG* Amplitude-integrated electroencephalography, *Bayley-III-NL* Bayley Scales of Infant and Toddler Development - Third Edition - Dutch Norms, *BMI* body mass index, *CCHD* critical congenital heart disease, *CPB* cardiopulmonary bypass, *IQR* interquartile range, *MRI* magnetic resonance imaging, *NIRS* near-infrared spectroscopy, *SD* standard deviation

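### The redox outcome's postnatal time point is cord blood taken before the first dose: it is a baseline, not a treatment comparison, and the redox effect of the two early doses cannot be isolated

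*Protocol article*

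**What the plan says.** The Redox state section describes extra blood and urine sampling at the Rotterdam and Utrecht centers, at "umbilical cord, preoperatively, 6 h postoperatively, and on days 1, 2, and 4 postoperatively". The redox row of Table 1 agrees and groups the same samples as "Postnatal (umbilical cord) Perioperative (directly before surgery and 6 h, 1 day, 2 days, and 4 days after surgery". The cord sample is thus the only one under the postnatal label.

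The text introducing the table states: "The secondary outcomes that will be compared between the allopurinol and mannitol-placebo groups are presented in Table 1". The redox row is aggregated by mean or median per group. Unlike the rows for brain injury, white matter volume, echocardiography and cerebral oxygenation, it lists no change between time points. The Secondary analysis section names unadjusted two-group tests only.

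In the prenatal group, study drug is given "early postnatally (within 45 (max. 60) min after birth and 12 h after the first dose), preoperatively (12 h prior to cardiac surgery"), then at the start of bypass and 24 h after surgery. Infants diagnosed after birth "will only receive the pre-, intra-, and postoperative doses of allopurinol PFI or mannitol-placebo PFI".

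**The concern.** A time point at which no infant has been treated is listed among the times at which an outcome is compared between arms. The same row also lists allopurinol and oxypurinol levels, for which a between-arm comparison before any dose has no meaning. Nothing in the row or in the Secondary analysis section gives the cord value the role it could usefully play, that of a baseline.

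The second issue is coverage. The Background argues that treatment should begin early after birth as well as around surgery, and that MRI before and after surgery is needed to evaluate the two treatment periods separately. The Discussion names the time shortly after birth as one of two vulnerable periods. The Redox state section gives as its aim "In order to quantify and assess the antioxidant properties of allopurinol after ischemia-reperfusion events" and does not limit this to surgery. The MRI schedule separates the two periods; the redox schedule does not. A reader of the results could take the absence of a postnatal redox difference as evidence about the early doses, which it cannot be.

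**Working it through.** The plan gives no figure to reproduce, and no power or alpha calculation bears on the point. The check places dosing and redox sampling on one timeline.

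**Inputs.** Dose times come from the Prenatal group and Postnatal group sections. Redox times come from the Redox state section and Table 1. That cord blood precedes dose 1 is inferred from dose 1 being given to the infant after birth.

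**Prenatal group**

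| Time | Event | Doses received |
|---|---|---|
| about 0 h | redox sample 1 (cord) | 0 |
| by 0.75 h, at most 1 h | dose 1 | 1 |
| by about 1 + 12 = 13 h | dose 2 | 2 |
| surgery − 12 h | dose 3 | 3 |
| just before surgery | redox sample 2 | 3 |
| start of bypass | dose 4 | 4 |
| 24 h after surgery | dose 5 | 5 |

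Redox samples 3 to 6 follow surgery, at 6 h and on days 1, 2 and 4. The number of redox samples between dose 1 and dose 3 is 0 of 6.

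**Cord contrast.** With zero doses in both arms, randomization gives E[cord, allopurinol] − E[cord, placebo] = 0 for every marker, whatever the drug's true effect.

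**Pre-surgery contrast.** In the prenatal group the arms differ by doses 1, 2 and 3. The randomized difference estimates the joint effect of all three. Writing it as (effect of doses 1 and 2) + (effect of dose 3, given doses 1 and 2) leaves one estimate for two unknowns. Postnatal-group infants have had only dose 3 at this sample, but comparing them with prenatal-group infants (one dose against three) is not a randomized comparison. The Discussion itself describes the postnatal group as often admitted with respiratory and circulatory insufficiency.

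**Time since dose 2 at redox sample 2.** The day of surgery is not fixed. Assuming day 4 or day 7, the limits of the preoperative MRI window, or the 4-week eligibility limit:
- day 4: 96 − 13 = 83 h
- day 7: 168 − 13 = 155 h
- 4 weeks: 672 − 13 = 659 h

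On each assumption, dose 3 lies only 12 h before surgery.

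**Other early samples.** The pharmacokinetic row of Table 1 has postnatal draws from 15–60 min to 96–168 h after birth. "In the first 24 neonates with a prenatal CCHD diagnosis in the UMC Utrecht, blood samples will be collected postnatally and perioperatively", and about 12 of these infants are expected in each arm. The assays cover the drug and its metabolite, plus xanthine, hypoxanthine and uric acid. They include none of the ELISA redox markers.

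Figure 2, the participant timeline, is not shown in the text available and could not be checked.

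**The case against.** The strongest reply is that the schedule suits its purpose. Five of the six samples lie around surgery, where ischemia and reperfusion are expected. Nothing in the Redox state section promises to isolate doses 1 and 2, and text and table agree. The postnatal label may simply be a way of sorting sampling times, since the pharmacokinetic row also puts cord blood there, where it can only be a pre-dose value. Baseline use is compatible with the text, and detailed biomarker modelling may sit in a document not shown.

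Much of this stands. There is no internal contradiction, and an extra early sample is largely a design preference. It does not remove the labelling problem. Table 1 is introduced as the list of outcomes compared between arms, and the only methods stated are unadjusted tests, so the article as written gives cord values the status of an outcome.

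A reader might infer more than the documents support:
- **That the early doses leave no trace in the redox data, or that the substudy informs only the perioperative doses.** The pre-surgery contrast is randomized and, in the prenatal group, cumulative over doses 1 to 3. Any residual effect of the early doses is in it but cannot be separated.
- **That early biology goes unobserved.** Purine and uric acid levels bear on xanthine oxidase inhibition after doses 1 and 2, though indirectly.
- **That 188 of 236 infants are affected.** Those are trial-wide figures. Redox sampling covers two centers, and the cohort size is not given.
- **That testing cord values at 5% yields about one false positive per 20 markers.** No separate test at the cord time point is specified.

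**Conclusion.** The point holds in a limited form. The comparison at the only postnatal redox time point has expected value zero and carries no information on the drug. With 0 of 6 redox samples between dose 1 and dose 3, the redox effect of the two early doses cannot be isolated, although it may contribute to the pre-surgery contrast.

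This rests on cord blood being drawn before dose 1, which the dosing schedule makes safe to assume, and on the schedule being complete as stated in both places. The consequence is confined to a secondary biomarker outcome at two centers. The primary analysis, its error control and its power are untouched.

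**What to change.** 1. In the redox row of Table 1, list the cord sample as the pre-dose baseline of the prenatal group, and do not report it as a treatment comparison.
2. Use the cord value as a baseline covariate for the later redox values in prenatal-group infants at the two redox centers. The precision gained depends on the correlation between cord and later values, which the documents do not give.
3. State that the substudy does not isolate the redox effect of the early postnatal doses.
4. Optionally, if stored volume and sample handling allow, run the redox panel on one postnatal pharmacokinetic sample already scheduled for the Utrecht infants (for example the 24 h draw, about 24 − 13 = 11 h after dose 2) and label it exploratory.

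Items 1 to 3 cost wording and a simple adjusted model, with no new sampling. Item 4 needs no new draw but up to 24 × 1 = 24 panel runs, each covering five ELISA domains and mass spectrometry. It would rest on about 12 infants per arm. Since enrolment began in February 2020, these infants may already have been sampled, and the documents do not say what plasma remains or how it was handled.

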### Statistical analysis

#### Primary analysis

The primary analysis will be the *Z*-test for the difference of proportions between the allopurinol group and mannitol-placebo group on the primary composite endpoint. This primary analysis will be performed on the total study population and the subgroup of neonates with a prenatal diagnosis of CCHD, where significance for the prenatal group is only declared if the overall result has been demonstrated.

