### Study setting

The trial will be conducted in 4 academic centers for CHD in the Netherlands: University Medical Center (UMC) Utrecht (sponsor), UMC Groningen, and Academic Center for Congenital Heart Disease (ACAHA) in Erasmus Medical Center (MC) Rotterdam and Radboudumc Nijmegen.

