#### Randomization and allocation concealment

Randomization will be performed by Ace Pharmaceuticals in blocking for both the prenatal and postnatal diagnosis group (by Randlist version 1.2 software). Stratification will be conducted per center and for a prenatal diagnosis or postnatal diagnosis of CCHD. The first available box of blinded study medication will be allocated by the study team to consecutive study subjects. Each box will be labeled with a unique medication identification number, which enables identification of treatment allocation for data analyses afterwards or emergency unblinding.

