#### Sample size

The sample size is calculated based on an assumed reduction in (absolute) incidence of 20% in the more prevalent subgroup of prenatal diagnosis (± 80% of the total population, control event rate assumed 71%) and a reduction of 9% in the postnatal diagnosis group (± 20% of the population, control event rate assumed 55%). With a total sample size of 236 CCHD neonates, of which 188 in the prenatal subgroup and 48 in the postnatal subgroup, the study has approximately 80% power to demonstrate the advantage of allopurinol in the total group with a two-sided alpha of 5%. The power of the hierarchical testing strategy is only slightly affected, given the large proportion of the prenatal group (80%). The effect sizes are a relevant and viable expectation and are based on the results of previous neuroprotective studies on head cooling in neonatal encephalopathy and perioperative allopurinol administration in CCHD neonates [26, 59]. RStudio version 3.6.1 was used for the sample size analysis.

Participants will be substituted in the following cases: (1) when cardiac surgery with CPB in the first month of life is unexpectedly not required or (2) when there is consent withdrawal before postoperative MRI. It is to be expected that these cases rarely occur.

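### The primary Z-test ignores the factors that randomisation is stratified by: a valid test, but slightly conservative, and easily aligned with the design

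*Protocol article*

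**What the plan says.** Under Randomization and allocation concealment: "Stratification will be conducted per center and for a prenatal diagnosis or postnatal diagnosis of CCHD". Allocation is in blocks. Under Study setting: "The trial will be conducted in 4 academic centers for CHD in the Netherlands". That makes up to eight centre-by-diagnosis cells.

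Under Primary analysis, the method is a Z-type "test for the difference of proportions between the allopurinol group and mannitol-placebo group on the primary composite endpoint". Its scope is also fixed: "This primary analysis will be performed on the total study population and the subgroup of neonates with a prenatal diagnosis of CCHD". The prenatal result can be declared significant only after the overall result. No stratum or covariate is named.

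Under Sample size, the two diagnosis groups are given different risks: "80% of the total population, control event rate assumed 71" per cent with a 20-point absolute reduction, and "20% of the population, control event rate assumed 55" per cent with a 9-point reduction. The plan continues: "With a total sample size of 236 CCHD neonates, of which 188 in the prenatal subgroup and 48 in the postnatal subgroup". Power is put at approximately 80% with a two-sided alpha of 5%.

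**The concern.** Blocking within strata balances the arms on the stratification factors. If those factors predict the outcome, the difference between arms varies less than under simple randomisation. A crude two-proportion Z-test does not use this: its variance still contains the between-stratum spread that the design has removed. Its true type I error then falls below the nominal level and some power is lost.

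The plan's own assumptions make diagnosis group prognostic. Centre may be prognostic too. Care follows each centre's routine, and one component of the endpoint (too unstable for postoperative MRI) is decided by the local clinical team. With power planned at about 80%, there is little margin to spare. The question is how much is lost.

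**Working it through.** **Inputs.** From Sample size: 188 prenatal neonates (control 71%, allopurinol 71 − 20 = 51%) and 48 postnatal (control 55%, allopurinol 55 − 9 = 46%). Equal allocation gives 118 per arm (94 + 24). The final alpha is taken as 0.05; the article gives no figure for the adjusted level, and 0.049 moves each power below by about 0.3 points.

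**Step 1: reproduce the stated power with the crude test.**
- Control: (188 × 0.71 + 48 × 0.55)/236 = 0.6775
- Allopurinol: (188 × 0.51 + 48 × 0.46)/236 = 0.4998
- Difference d = 0.1776; mean rate 0.5886
- SE under the null: √(2 × 0.5886 × 0.4114/118) = 0.0641
- SE under the alternative: √[(0.6775 × 0.3225 + 0.4998 × 0.5002)/118] = 0.0630
- Power = Φ[(0.1776 − 1.96 × 0.0641)/0.0630] = 79.6%

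This matches the plan, so the sample size and the stated analysis agree.

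**Step 2: stratify by diagnosis only, on the plan's own rates.** The weights are 188/236 = 0.797 and 48/236 = 0.203. The estimate is unchanged: 0.797 × 0.20 + 0.203 × 0.09 = 0.178. The between-stratum variance that drops out is 0.797 × 0.203 × (0.71 − 0.55)² = 0.0041 per control patient and 0.797 × 0.203 × (0.51 − 0.46)² = 0.0004 per allopurinol patient, out of about 0.22 and 0.25.

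| | Crude | Stratified by diagnosis |
|---|---|---|
| SE, alternative | 0.0630 | 0.0627 (ratio 0.995) |
| 95% CI half-width, points | 12.4 | 12.3 |
| Power | 79.6% | 79.9% |
| Total N for 80% power | 239–240 | 237–238 |

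The gain is about 0.5% in SE, 0.3 points of power, or two patients. The prenatal test lies within one diagnosis group, so only centre is ignored there.

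**Step 3: add centre.** The protocol gives no event rates by centre, so this step rests on assumptions: four equal centres (per arm 24/24/23/23 prenatal and 6 in each postnatal cell), arms exactly balanced within cells, and centre effects evenly spaced on the log-odds scale. There were 200,000 simulated trials per row. The stratified test is Cochran-Mantel-Haenszel (CMH) by centre and diagnosis.

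| Centre log-odds range (assumed) | Prenatal control rates | Power, crude | Power, stratified | Type I error, crude | Type I error, stratified |
|---|---|---|---|---|---|
| 0 | 71% throughout | 80.7% | 80.5% | 4.8% | about 5% |
| ±0.3 | 64–77% | 80.0% | 80.0% | 4.7% | about 5% |
| ±0.6 | 57–82% | 77.9% | 78.5% | 4.4% | about 5% |
| ±1.0 | 47–87% | 72.6% | 75.5% | 3.6% | about 5% |

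The cost of ignoring the strata is the gap between the two power columns. The fall down each column also reflects the changed event rates, which affect both tests.

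**Step 4: do these figures carry over to a risk difference?** With n per arm in each cell, the CMH numerator is Σ(x_C − m/2), where m = x_C + x_T. This equals Σ n(p_C − p_T)/2, or 118/2 times the Mantel-Haenszel risk difference. The two tests share a numerator and differ only in the variance estimate.

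**The case against.** The strongest reply is that nothing is wrong. The crude test holds its level, the sample size was computed for it, and on the protocol's own rates the confidence interval narrows by 0.1 point. That stands, and it sets the weight of this point.

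Three stronger readings are tempting, and the documents support none of them.
- **An invalid test or inflated type I error.** The direction is the opposite: the crude test errs on the conservative side.
- **A material loss of power.** This needs large differences between centres. The article says that care follows local routine and that scanners are 1.5 or 3.0 T. It does not say that event rates differ as a result, or that field strength varies by centre. Postoperative scans are read centrally and blinded, which removes local reader differences. The local judgement of instability remains a possible source, of unknown size.
- **Harm from incomplete blocks in small postnatal cells.** Block size is not given, and the simulations hold every cell in balance, so they say nothing about this.

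An analysis plan that is not shown may add adjusted analyses. That does not settle the matter, because the article names the primary test itself. It is also fair that a CMH chi-square does not pool directly across the multiple imputations planned for missing data; the fix has to allow for that.

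**Conclusion.** The mismatch between design and analysis is real, and its known cost is small: about 0.5% in standard error and at most about 0.3 points of power, on the protocol's own rates. Anything larger depends on centre differences that the protocol does not report. Under the assumptions above the loss is nil at a 13-point range of prenatal control rates, about half a point at a 25-point range (57–82%), and about 3 points at a 40-point range (47–87%). The last should be read as an extreme. The change is worth making because it costs almost nothing and holds the level near 5% in every scenario run, not because the present test is wrong.

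**What to change.** Make the primary analysis a Mantel-Haenszel or stratum-weighted risk difference by the randomisation factors, with its standard error, 95% confidence interval and Z-test. Use centre by diagnosis for the total population and centre for the prenatal group. Apply it at interim and final, and keep the crude Z-test as a sensitivity analysis. An estimate with a standard error can be combined across the multiple imputations.

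Name the variance estimator as well. The plug-in p(1 − p)/n in a cell is on average (n − 1)/n of the true value: 23/24 in a prenatal cell of 24 per arm, but 5/6 in a postnatal cell of 6. A divisor of n − 1, or the CMH null variance for the test, avoids that understatement.

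Cost: no patients and no data. The test is fixed in the protocol and recruitment has begun, so the change is a protocol modification that needs approval, and it must be made before unblinding. If centres are in truth identical, about 0.2 points of power are lost at the final analysis, and in a separate simulation the chance of crossing the interim boundary was about 0.5 points lower.
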